## Abstract

**Background:**

Cardiac surgery is one of the most commonly performed surgical procedures worldwide with >700,000 surgeries in 2006 in the US alone. Cardiac surgery results in a considerable exposure to physical and emotional stress; stress-related disorders such as depression or post-traumatic stress disorder are the most common adverse outcomes of cardiac surgery, seen in up to 20% of patients. Using information from a genome-wide association study to characterize genetic effects on emotional memory, we recently identified a single nucleotide polymorphism of the glucocorticoid receptor gene (the Bc*l*l single nucleotide polymorphism) as a significant genetic risk factor for traumatic memories from cardiac surgery and symptoms of post-traumaticstress disorder. The Bc*l*l high-risk genotype (Bc*l*l GG) has a prevalence of 16.6% in patients undergoing cardiac surgery and is associated with increased glucocorticoid receptor signaling under stress. Concomitant animal experiments have confirmed an essential role of glucocorticoid receptor activation for traumatic memory formation during stressful experiences. Early cognitive behavioral intervention has been shown to prevent stress-related disorders after heart surgery.

**Methods/Design:**

The proposed study protocol is based on the above mentioned earlier findings from animal experiments and preclinical studies in volunteers. Patients (n = 872) will be genotyped for the Bc*l*l single nucleotide polymorphism before surgery, which should result in 120 homozygous high-risk carriers of the Bc*l*l GG allele and 240 randomly selected low-risk heterozygous or non-carriers of the single nucleotide polymorphism. All patients will then undergo randomization to either cognitive behavioral intervention or a control intervention consisting of non-specific general information about the role of stress in heart disease. The primary efficacy endpoint will be post-traumatic stress levels at one year after surgery as determined by a standardized questionnaire that has been specifically validated in patients after critical illness.

**Discussion:**

The proposed randomized controlled trial intends to demonstrate that a preoperatively administered minimal cognitive behavioral intervention targeted to homozygous carriers of the Bc*l*l *G high-risk allele reduces traumatic memories and post-traumatic stress disorder symptoms after heart surgery to a level seen in non-carriers of the mutation, and thus improves the neuroemotional outcome of cardiac surgery.

**Trial registration number:**

The trial will be registered at http://www.clinicaltrials.gov/ before commencing with the study.

## Background

Cardiac surgery (CS) is one of the most frequent surgical procedures worldwide with more than 700,000 cardiovascular procedures performed in 2006 in the US alone [1]. Surgery and the subsequent intensive care unit (ICU) therapy represent a considerable physical and emotional stressor [2]. Whereas physical functioning after CS improves over time, mental disorders as a result of high perioperative stress such as chronic anxiety, depression or post-traumatic stress disorder (PTSD) can persist for months and years [2,3]. Up to 20% of patients develop PTSD symptoms after CS [3]. Post-traumatic stress in the presence of heart disease is linked to impaired health-related quality of life [4], reduced rate of return to professional activities, increased health-care utilization with considerable cost for health-care systems [5] and a poor long-term cardiovascular prognosis [6]. However, although efficient treatments of PTSD exist, little is known about preventing PTSD and other stress-related disorders through evidence-based interventions in critically ill patients undergoing CS or intensive care therapy for other reasons. Therefore, targeted and cost-effective interventions to improve the neuroemotional outcome of extensive medical procedures are urgently required [7].

In this randomized controlled trial, we intend to use an innovative and personalized approach by identifying carriers of a genetic risk factor (Bc*l*l *G) for chronic stress after CS and investigate whether a targeted minimal behavioral intervention can counteract this genetic vulnerability for PTSD symptoms and improve long-term mental health.

### The Bc*l*l SNP of the glucocorticoid receptor influences traumatic memories and PTSD stress symptoms in patients undergoing cardiac surgery

The major risk factor for PTSD development in critically ill patients is the presence of traumatic memories from highly stressful experiences during ICU treatment [2,8]. Animal experiments performed by our research group and others have repeatedly shown that the encoding of traumatic experiences into emotional memory during stress is facilitated by a stress-induced increase in glucocorticoid [9] and endocannabinoid signaling [10]. Using information from a genome-wide association study to characterize genetic effects on emotional memory in volunteers (Figure 1), we have recently identified an intronic SNP of the glucocorticoid receptor (GR) gene (the Bc*l*l SNP) in patients undergoing CS that is associated with increased cortisol sensitivity of the GR and, thus, enhanced glucocorticoid signaling under stress. The increased cortisol sensitivity is seen in homozygous carriers of the Bc*l*l *G allele, which has a prevalence of 14% in the western European population [11] and 16.6% in our patients undergoing CS [12]. Homozygous carriers had a significantly increased risk for traumatic memories and PTSD symptoms of chronic anxiety, pain, depression and impaired health-related quality of life after CS [12]. We very recently confirmed this finding in a second study in an independent group of patients having CS (unpublished, Figure 2). In combination, these well-corroborated findings allow the preoperative identification of patients at risk for PTSD symptoms after heart surgery who could benefit from preventive interventions.

**Figure 2 F2:**
[figure not shown]
**PTSD stress symptom scores according to Bc*****l*****l genotype one week after discharge from the intensive care unit in a recent confirmatory study in patients undergoing cardiac surgery (n = 95).** **P* = 0.02 compared to non-carriers (CC) of the SNP (one-way analysis of variance with Holm-Sidak post-hoc test). Data represent means ± standard error of the mean (unpublished). PTSD, post-traumatic stress disorder.

### A cognitive behavioral intervention is effective in preventing PTSD symptoms after intensive care therapy

Although counterintuitive, increased analgesia and sedation of critically ill patients intended to prevent traumatic experiences during ICU treatment has not been successful in avoiding PTSD but has shown the opposite effect [13]. By contrast, a number of early interventions based on cognitive behavioral intervention (CBI) have been effective in improving the neuroemotional outcome of critical illness. A study in patients having CS showed that preoperative CBI (for example, explaining cardiac myths and misconceptions, detailing what to expect during the hospital stay and subsequent recovery period) improved physical function and depression after surgery [14]. Early psychological intervention in patients during ICU treatment by trained psychologists resulted in a lower incidence of PTSD symptoms and a lower use of psychotropic medication during follow-up [15]. The use of an intensive care diary, which has comparable effects to CBI by changing how patients think about their illness as they reread the story and build an autobiographical memory, has also been effective in reducing PTSD symptoms in patients after ICU therapy [16]. A detailed explanation of the forthcoming events during CS and ICU care will enhance the predictability of the events and thereby reduce feelings of anxiety, helplessness and life-threat. Evidence from both animal [17] and human [18] research clearly indicates the detrimental effects of unpredictable stress, whereas anticipated stress exhibits a milder impact on both psychological and physical health. A preoperative CBI enhances predictability and should therefore reduce the arousal during and directly after surgery in the ICU and, consequently, the release of excessive amounts of stress hormones and endocannabinoids (ECs) [10] that contribute to the hyperconsolidation of this potentially traumatic situation. Secondly, prominent theoretical models of PTSD propose a dissociation between hyperconsolidated emotional memories and poorly consolidated autobiographical context memories as the root cause of intrusive memories in PTSD [19,20]. Therefore, a preventive CBI should provide detailed context information prior to CS and shortly after CS, to locate potential traumatic experiences in time and space. Although previous studies have demonstrated that CBI has benefits in improving the neuroemotional outcome of critical illness, none of the earlier investigations were aimed specifically at patients with a genetically identified risk. By contrast, we hypothesize that a preoperatively administered minimal behavioral intervention targeted to carriers of a genetic risk factor (Bc*l*l GG) will reduce the risk for development of PTSD to that of non-carriers of the allele. This approach would be analogous to a prophylactic immunization of individuals with a well-characterized risk for an infectious disorder.

## Methods/Design

### Intervention scheme/trial flow

The flow of events during the study is depicted in Figure 3. After admission to the cardiac surgical ward, patients eligible for the study will be asked whether they are willing to participate. Patients will be told that if they agree to take part in the study, they can expect the following to take place. They will undergo genetic testing to identify a genetic risk within the stress hormone system for chronic stress reactions after surgery. They will then be randomized to either Intervention A, which provides specific information on postoperative procedures and focuses on possible and unexpected stressful experiences while in the ICU (the minimal behavioral intervention), or to Intervention B, which gives more general information about the role of stress during the perioperative period of CS.

**Figure 3 F3:**
[figure not shown]
**Flow chart showing the sequence of events and key points of decision making during the proposed study.** Rounded rectangles indicate tasks to be performed by medical personal (for example, the study physicians). Ovals represent the responsibilities of a study psychologist and his or her team.

After providing written informed consent, blood drawing for genotyping and an evaluation of cognitive ability will follow using the Mini Mental State Examination. Before randomization to either the intervention or the control group, the patients will be asked to complete a set of validated questionnaires to evaluate PTSD stress symptoms, standardized disease-related traumatic memories, depression, health-related quality of life, and current anxiety and pain. Randomization will be followed by the intervention, performed by a psychologist. After surgery, the patients will be admitted to the cardiovascular ICU. While in the ICU (postoperative days 1 to 4), the patients will be evaluated every 8 hours for sedation, delirium, pain and anxiety. Treatment variables will be recorded. One week after discharge from the ICU, the patients will be approached again by the study psychologist and asked to complete the set of questionnaires on traumatic memories from the ICU and post-traumatic stress intensity as well as current anxiety and pain symptoms. Six and 12 months after surgery, the patients will be interviewed by phone and will be sent the set of questionnaires by mail.

The primary efficacy endpoint of the study is a reduction in post**-**traumatic stress measured by questionnaire 12 months after surgery. The primary hypothesis to be tested is that this reduction is more pronounced for high-risk homozygous Bcll SNP carriers compared to the remaining patients.

### Data collection

Collected data will include demographic factors, objective indicators of myocardial function and severity of coronary artery disease, current pharmacologic treatment and dosage, cardiovascular risk factors, medical comorbidities, mental health history, episodes of high stress exposures related to the current hospitalization, recurrent symptoms of coronary heart disease, recurrent hospitalizations, compliance with medication, and type and intensity of rehabilitation after CS.

### Inclusion criteria

•Planned CS for coronary artery bypass grafting or valvular heart disease using cardiopulmonary bypass

•age >18 years

•sufficient knowledge of the German language in written and oral comprehension

•Western European origin (according to information provided by the patient).

### Exclusion criteria

•CS involving cardiocirculatory arrest under controlled hypothermia

•unstable preoperative cardiovascular condition requiring emergency procedures

•severe alcohol or drug abuse

•major pre-existing neurologic or psychiatric diseases (for example, PTSD, major depressive/bipolar or somatoform disorder)

•previous CS or treatment in an ICU with the exception of brief stays in a coronary care unit

•cognitive impairment as determined by the nine-item short version of the Mini Mental State Examination

•chronic organ dysfunction (renal, liver or lung)

•severe comorbidities likely to cause death within one year (for example, cancer)

•preoperative use of glucocorticoids (for example because of rheumatism)

### Selection of study population

The effect of the Bc*l*l SNP on post-traumatic stress and cortisol signaling has been characterized in patients undergoing CS at our institution who fulfilled the abovementioned criteria [12]. Patients satisfying the entry criteria of our study are in every aspect comparable to patients attending other European CS centers [21]. In addition, our study is a multi-center study with two centers (Klinikum Grosshadern and Herzklinik Augustinum, both in Munich). One can therefore assume that the results of our suggested study can be generalized.

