### Statistical analyses

#### Sample size calculations

In several previous studies in CS patients, we assessed post-traumatic stress using the PTSS-10 instrument that will also be the primary outcome measure in this study. Our preliminary work indicated an 8-point difference on the PTSS-10 scale between homozygous Bc*l*l *G carriers as opposed to non-carriers [12]. This study also showed that the PTSS-10 score did not significantly decrease until six months after surgery. We may assume that the non-trauma-focused control intervention does not change post-traumatic stress levels in homozygous patients and that the difference of 8 points in post-traumatic stress scores between non-carriers and homozygous individuals is clinically meaningful. This assumption is supported by the recent study discussed in the section *Primary endpoint*[26] that showed that even a relatively low PTSS-10 score (>20) in patients one week after ICU therapy and weaning from mechanical ventilation was highly predictive for the later development of PTSD. Based on the results of our pilot study [12], we make the following assumptions: first, the mean PTSS-10 score one year after ICU discharge is 18±8 (mean ±SD) for non-Bc*l*l *G carriers and heterozygous Bc*l*l *G carriers and 25±8 for homozygous Bc*l*l *G carriers each under control intervention. Second, the mean PTSS-10 score one year after ICU discharge is 18 ±8 for all patients under experimental intervention. Both assumptions show a quantitative intervention-SNP interaction. An overall sample size of 252 patients (84 per SNP group) is needed assuming a type I error rate of 5% and a type II error rate of 80% to detect a statistically significant differential treatment effect between the genotype groups. The sample size calculation was performed by Nquery (Statistical Solutions Ltd.,[name]). Further, experience from former studies shows a perioperative mortality of 8% and a loss to follow-up of approximately 20% of patients at the six-month time point [2,12]. Adjustment for a drop-out rate of 30% leads to a total of 120 required patients (120–0.3 × 120 = 84) per SNP group. In our previous study in 126 Western European CS patients from our institution, 43% were non-carriers of the Bc*l*l *G, 43% were heterozygous Bc*l*l *G carriers and 14% were homozygous [12]. This means that we will have to genetically screen approximately 872 patients to detect 120 homozygous individuals eligible for randomization. Genetic screening will also result in the identification of approximately 376 non-carriers and 376 heterozygous individuals. These patients will also be randomly allocated to the control and the targeted intervention group but, to reduce costs, only 120 individuals with each genotype will be randomly selected by choosing every third consecutive heterozygous or non-carrier patient included in the study. Thus, we will have to screen and genotype 872 patients to include 360 patients into the final analyses (Figure 4).

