#### Secondary endpoints

As the secondary endpoints are collected at four different times, we will use LME models (which respect the correlation of the observations within a patient evolving over time) and study the main and interaction effects of the intervention and the SNP groups on the (possibly adequately transformed) endpoints. Appropriate imputation techniques will be used to handle missing values (results of the LME model can help to impute the primary endpoint based on the patient’s time course before dropping out, points missing in the longitudinal data can also be imputed) [45]. The analysis will be performed using the statistical software environment R [46].

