## Discussion

Progress in the field of ICU therapy and medical procedures such as CS has resulted in improvements in short- and long-term survival rates in critically ill patients. This progress is, however, met by an in increasingly older population with increased life expectancy and multiple comorbidities requiring extensive surgical procedures and treatment in ICUs. By now, there are more than 10,000 critically ill patients treated in >1,500 ICUs on any given day in Europe [48] and CS is one of the most common surgical procedures performed worldwide. This imbalance between demand, disease severity and the required efforts for cost containment makes it unlikely that further progress in surgical performance and life support techniques in the ICU will result in meaningful improvements in long-term outcomes of critically ill patients with heart disease requiring surgery. There is increasing evidence that post-traumatic stress associated with critical illness and ICU therapy has long-lasting negative consequences on health-related quality of life, cognitive and social functioning, health-care utilization and even long-term mortality [2,49]. Published evidence also shows that behavioral interventions are able to prevent the development of post-traumatic stress symptoms related to exposure to a range of different malignant stressors including CS [14,50]. The overarching aim of the proposed project is to demonstrate that a targeted, CBI reduces the intensity of post-traumatic stress in patients undergoing CS and results in clinically meaningful improvements in long-term outcomes six and twelve months after surgery.

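### GG carriers make up one third of the analysed sample but 14–16.6% of the source population, so an unweighted pooled intervention effect does not carry over to cardiac surgery patients if the effect differs by genotype

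*Protocol article*

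**What the plan says.** Under Selection of study population, the protocol article argues from the similarity of eligible patients to those at other European centres, and from having two centres, that "One can therefore assume that the results of our suggested study can be generalized". Genotype is not mentioned there.

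Under Sample size calculations, all GG patients are kept. For the other two genotypes, "only 120 individuals with each genotype will be randomly selected by choosing every third consecutive heterozygous or non-carrier patient included in the study". The section concludes: "Thus, we will have to screen and genotype 872 patients to include 360 patients into the final analyses". The source distribution given there is 43% non-carriers, 43% heterozygous and 14% homozygous. The Background gives a GG prevalence of 16.6% in the group's cardiac surgery patients.

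Under Primary analysis, the intervention-by-genotype interaction is assessed first, then differential treatment effects between pairs of genotypes. Under Statistical analyses, Secondary endpoints, the mixed models will "study the main and interaction effects of the intervention and the SNP groups". No population weighting is described.

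The Discussion states the overarching aim as showing that the intervention "reduces the intensity of post-traumatic stress in patients undergoing CS and results in clinically meaningful improvements in long-term outcomes".

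**The concern.** Sampling on genotype is a sensible way to power an interaction test. It also means that any quantity averaged over genotypes describes a constructed one-third-GG mix. The article plans such quantities (main intervention effects on the secondary endpoints), says without qualification that results generalise, and words its aim for cardiac surgery patients as a whole. A reader who takes an overall effect on depression, quality of life or traumatic memories from the fitted model, together with the generalisation statement, would apply it to a population with less than half the share of GG carriers. If benefit is concentrated in GG, as hypothesised, the overall benefit in that population would be overstated.

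**Working it through.** **Inputs** (Sample size calculations unless noted)
- Control-arm PTSS-10 at one year: 25 in GG, 18 in the other two genotypes. Experimental arm: 18 in all. SD 8.
- Implied effects: 25 − 18 = 7 points in GG, 18 − 18 = 0 in the others.
- Analysed sample: 120 per genotype. Source: 43/43/14%. GG prevalence is 14%, or 16.6% in the Background.
- Assumed: two-sided 5% test (sidedness is not stated), 80% power, and equal drop-out across genotypes, so that the 1:1:1 mix persists to one year.

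**The plan's own figures.** A pairwise interaction contrast is a difference of two treatment differences (7 versus 0), with variance 4 × 8²/m for m patients per cell. Two-sided 5% and 80% power give m = 42, hence 84 per genotype and 3 × 84 = 252. Drop-out: 84/0.70 = 120. Screening: 120/0.14 = 857, close to the stated 872. Sampling fraction in the other genotypes: 120/376 = 32%. The planning effects of 7, 0 and 0 are therefore the ones that the design rests on.

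**Pooled effect, equal weights.** (7 + 0 + 0)/3 = 2.33 points.

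**Pooled effect, population weights**
- 14% GG: 0.14 × 7 = 0.98; ratio 2.33/0.98 = 2.38.
- 16.6% GG: 0.166 × 7 = 1.16; ratio 2.33/1.16 = 2.01.

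**Control-arm mean.** Equal weights: (18 + 18 + 25)/3 = 20.3. Population: 18 + 0.14 × 7 = 19.0, or 18 + 0.166 × 7 = 19.2.

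**Dependence on the effect in the other genotypes.** Write d_GG for the GG effect, d_o for the average effect in the other two, and p for GG prevalence. Non-carriers and heterozygotes are equally common in the source and in the sample, so only their average matters. The distortion is (1/3 − p)(d_GG − d_o). At d_GG = 7 and d_o = 0 this is 1.35 points (p = 0.14) or 1.17 points (p = 0.166). With d_GG = 7 and assumed values of d_o:

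| d_o | Equal weights | Population, 16.6% / 14% GG | Ratio |
|---|---|---|---|
| 0 | 2.33 | 1.16 / 0.98 | 2.01 / 2.38 |
| 1 | 3.00 | 2.00 / 1.84 | 1.50 / 1.63 |
| 2 | 3.67 | 2.83 / 2.70 | 1.30 / 1.36 |
| 3.5 | 4.67 | 4.08 / 3.99 | 1.14 / 1.17 |
| 7 | 7.00 | 7.00 / 7.00 | 1.00 / 1.00 |

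**Cost of weighting.** With equal variances for the three genotype-specific estimates, the variance of the weighted average is proportional to the sum of squared weights. Equal weights: 3 × (1/3)² = 0.333. Source weights: 2 × 0.43² + 0.14² = 0.389. Ratio 0.389/0.333 = 1.17, so the standard error rises by about 8% (√1.17 = 1.08).

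**The case against.** The strongest reply is that the trial's question is untouched. The primary hypothesis and analysis concern differences in effect between genotypes, and sampling on genotype distorts neither the interaction nor any genotype-specific effect. This stands in full.

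The generalisation sentence rests on comparability of patients and centres and never says that a pooled effect will be applied to everyone. The Discussion even expects no effect in the majority who do not develop stress-related disorders, and foresees tailoring the intervention to patients at risk. This softens the concern but does not remove it: the sentence is unqualified, and the overarching aim is worded for cardiac surgery patients generally.

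The numerical example is on PTSS-10, whereas the planned main effects are on secondary endpoints, for which no genotype-specific effects are assumed. That is correct, so the factor is an illustration and not an estimate for those endpoints. The meaning of a main effect also depends on factor coding, which is not stated. With sum-to-zero coding it is the equally weighted average. With a reference genotype and an interaction term it is the effect in that genotype alone. Neither is the population effect.

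A weighting rule may properly sit in the analysis plan, so its absence from an article is not itself a fault. The point rests on what the article does state: the sampling fractions, the main effects and the generalisation.

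Four stronger readings are tempting and not supported:
- That every overall effect will be 2.0 to 2.4 times too large. This requires zero effect outside GG, which is part of what the trial tests.
- That the distortion always favours the intervention. Its sign is that of d_GG − d_o; it vanishes with equal effects and reverses if the other genotypes benefit more.
- That the Hardy-Weinberg check fails by design. The genotyping section does not say that it is run on the 360 selected patients, and 872 are genotyped.
- That the entry criteria by themselves contradict the generalisation. They are openly listed, and the comparability statement is confined to patients who meet them.

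**Conclusion.** The concern holds in a limited form. A pooled intervention effect or arm mean taken unweighted from the 1:1:1 sample does not estimate the value in the cardiac surgery population when the quantity differs by genotype. Under the protocol's PTSS-10 planning values the pooled effect would be 2.33 points against 0.98 to 1.16. The factor shrinks to 1.30–1.36 if the other genotypes gain an assumed 2 points, and to 1.0 if all genotypes gain equally. The size for the secondary endpoints cannot be derived from the document. The sample size, the primary interaction test and the pairwise genotype contrasts need no change. This is a worthwhile correction to the reporting of overall effects and to one sentence on generalisation; it does not threaten the primary result.

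**What to change.** 1. Under Statistical analyses, Secondary endpoints: estimate any overall intervention effect or arm mean as the average of the three genotype-specific estimates, weighted by the genotype frequencies observed in all genotyped eligible patients (about 872). Label any unweighted figure as referring to the genotype-enriched sample.
2. Under Selection of study population: limit the generalisation statement to genotype-specific effects and to overall effects standardised in this way.
3. Leave the primary analysis as it is.

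The cost is a change of wording and one weighting step. Genotype is already determined in every screened patient, so no extra patients or measurements are needed. The variance of the pooled effect rises by about 17%, and under the trial's own hypothesis the reported overall effect will be smaller.
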